### Sample size calculation

2.8

The power analysis was carried out previously for the determination of the size of the study sample to offer 80% statistical power at an alpha level of 0.05%. After calculation, in each group, the size of sample of 50 patients is enough to measure the difference of CM score by at least 5 points at the end of 4 years, and 10% of data may be lost. Therefore, a total of 110 participants (55 per group) are enlisted for this research.

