## Introduction

1

With the continuous development and advances of surgical instruments and technology, open technology is gradually being replaced by arthroscopic repair, which can recover faster and obtain good cosmetic results in rotator cuff repair.^[1–3]^ Nevertheless, about 27% of cases will recur.^[4]^ The insufficient tendon-bone healing is regarded to be a significant cause of recurrence. Rotator cuff retear may also be affected via a number of factors, containing smoking, the index of body mass, age, tear size, type, location, the quality of tendon, surgical technique employed, fatty infiltration, and postoperative rehabilitation.^[5,6]^ Many complementary biologic therapies have been utilized for the improvement of the early tendon healing quality, and they may also decrease the incidence of the late tendon sequelae.^[7]^

Platelet-rich plasma (PRP), an autologous platelet concentrate (contain a large number of growth factors), has been widely investigated in healing and rebuilding the bone and tendon tissue.^[8–11]^ These growth factors possess a significant effect on the regeneration, repair, and acceleration of biochemical processes, thereby reducing pain caused by the tears of rotator cuff and promoting the healing of the rotator cuff.^[12–16]^ Many systematic reviews and meta-analysis have shown that the use of the PRP in repairing the rotator cuff can not obviously improve clinical result, but it can improve the structural healing of small to moderate tears.^[17–20]^ Currently, many clinical trials, which assessed the influence of the PRP on repairing the rotator cuff, have generally reported short-term results.^[21–24]^ Therefore, the randomized controlled studies containing the long-term follow-up are critical for the evaluation of the whole latent benefits of PRP.

The objective of this prospective randomized research is to study and then compare the long-term effectiveness of the repair of arthroscopic rotator cuff without and with the platelet-rich plasma. It is assumed that there is no difference in the clinical results between patients receiving the repair of arthroscopic rotator cuff and the patients who do not receive PRP enhancement.

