### Randomization

2.3

The randomization list was generated with the block randomized procedure. Participants were randomly allocated to one of two parallel combinations to receive either PRP or placebo (with the ratio of 1:1). In order to assign participants, an independent researcher who was not participated in surgery prepared a sealed and opaque envelope, which contains the treatment task. Subsequently, an uninformed researcher opened the envelope and assigned participants to either control group or PRP group on the basis of the chose index card.

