### Outcomes measures

2.7

All patients were evaluated at follow-up and baseline for the scores of Constant-Murley (CM) and American Shoulder and Elbow Surgeons (ASES), the numerical rating scale (NRS), and retear rate. The primary outcome is retear rate. The NRS of people are assessed for pain on an 11-point scale ranging from zero (for “no pain”) to 10 (for “most severe pain possible”). The ASES scores and CM scores are reliable, effective and responsive, and cover various activities of daily living to assess shoulder function, and the assessment are performed at baseline, 12 months, 24 months, and 48 months.

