### Statistical analysis

2.9

The standard deviation and mean are the descriptive statistics. The normality of all the data was detected via the Kolmogorov–Smirnov test. The difference of value before and after the treatment was calculated by the paired sample *t* test. The student *t* test was applied for the comparison of variances between study group and control group. The analysis is implemented with the SPSS 16.0 (SPSS Inc., Chicago, IL), the significance level remain at *P* < .05.

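### The stated 80% power belongs to the Constant-Murley score, not to the declared primary outcome, retear rate; with 50 per arm, halving a 27% retear rate would have about 40% power

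*Protocol article*

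**What the plan says.** Protocol article, Section 2.7 (Outcomes measures): "The primary outcome is retear rate". Each patient either has a retear or does not, so this is a comparison of two proportions. Constant-Murley (CM), ASES and pain scores are the other outcomes, with CM and ASES assessed at baseline, 12, 24 and 48 months.

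Section 2.8 (Sample size calculation): the calculation is meant "to offer 80% statistical power at an alpha level of 0.05" (the text prints a percent sign after 0.05), and in each group "50 patients is enough to measure the difference of CM score by at least 5 points at the end of 4 years". It allows that "10% of data may be lost" and concludes that "a total of 110 participants (55 per group) are enlisted for this research". Retear is not mentioned in this section.

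Section 1 (Introduction) gives the only recurrence figure in the article, as background: "about 27% of cases will recur".

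**The concern.** Power is a property of one comparison. Power to detect a 5-point difference in a continuous function score says nothing about power to detect a difference in a yes/no outcome. The article states both its primary outcome and its sample-size basis, and the two do not match. This is a contradiction in the text, not a detail left to a longer document, and no analysis plan could make the Section 2.8 figure apply to retear.

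What is at stake is how the result will be read. The Introduction and Discussion expect no difference in clinical results, and the Discussion promises information on whether PRP works. If the retear comparison has well under 80% power, a non-significant result is likely even when PRP has a worthwhile effect. It would agree with the stated expectation and seem to carry the authority of an 80% power claim. The Introduction itself cites reviews in which PRP improves structural healing of small to moderate tears, so a real effect on retear is plausible and could be missed.

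**Working it through.** **Inputs from the article**
- Allocation 1:1 (Section 2.3); 50 per group analysed, 55 per group enrolled (Section 2.8).
- Significance level 0.05. Section 2.9 says "the significance level remain at *P* < .05"; the 0.05% printed in Section 2.8 conflicts with this and is treated as a sensitivity case.
- Control retear rate 27% (Introduction).

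**Assumptions, because the article gives no figure**
- The 27% background rate applies to the control arm.
- Testing is two-sided.
- A halving, 27% to 13.5%, is the reference effect; other effects and control rates are shown below.

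**The plan's own figure.** The 50 per group cannot be reproduced, because no standard deviation for CM is given. Solving n = 2·SD²·(1.96 + 0.842)²/5² for n = 50 gives SD = 5 / (2.802 × √(2/50)) ≈ 8.9 points. With a literal two-sided alpha of 0.05% the implied SD is 5.8. The step from 50 to 55 is 50 × 1.1 (50/0.9 would give 56).

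**Power for retear, normal approximation.** With p₁ = 0.27 and p₂ = 0.135, the mean is p̄ = 0.2025.
- Standard error factor under no difference: √(2 × 0.2025 × 0.7975) = 0.568.
- Under the alternative: √(0.27 × 0.73 + 0.135 × 0.865) = 0.560.
- Power = Φ[(0.135 × √50 − 1.96 × 0.568) / 0.560] = Φ(−0.284) = 38.8%.

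**Power by exact enumeration** over two binomials, 50 per arm, two-sided 5%:

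| Control v PRP retear | Relative reduction | Chi-square | Fisher |
|---|---|---|---|
| 27% v 17% | 37% | 22.8% | 16.4% |
| 27% v 13.5% | 50% | 39.9% | 30.6% |
| 27% v 10% | 63% | 61.7% | 50.4% |
| 27% v 7% | 74% | 80.3% | 69.8% |
| 27% v 5% | 81% | 90.0% | 82.0% |

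**Sample size for a halving.** n = [(1.96 × 0.568 + 0.842 × 0.560) / 0.135]² = 137.9, so 138 per arm. Allowing for 10% loss, 138/0.9 gives 154 per arm, or 308 in total.

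**Sensitivity of the halving result**
- Other control rates (chi-square, 50 per arm): 15%, 23%; 20%, 30%; 40%, 60%; 50%, 75%.
- All 55 per arm analysed, 27% control: 43%. With 55 per arm and a 50% control rate: 79%.
- One-sided 5% (normal approximation): 51%.
- Alpha taken literally as 0.05% (normal approximation): about 3%.

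**The case against.** The mismatch itself is hard to dispute. The case on the other side concerns how much to make of it.

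- *The 27% is background, and a halving is a reviewer's choice.* Both are true. The figure comes from a source not shown and is not specific to patients aged 18 to 55 with complete tears. So 40% is conditional and should be quoted with its assumptions. The conclusion is less fragile: power for a halving stays below 80% at every control rate tried from 15% to 50%.
- *A large enough effect would be detected.* True: power is 62% for 27% v 10% and 80% for 27% v 7%. The warning that non-significance is the likely result applies to a halving or less, not to reductions of about three quarters. A halving is nonetheless a large effect, and it would be missed about 60% of the time.
- *The label may be wrong rather than the sample size.* The stated aim is long-term effectiveness and the hypothesis concerns clinical results, both of which fit CM at 4 years. Retear is called primary in one sentence, and the abstract names no primary outcome. This does not remove the contradiction, but it is a good reason to offer a change of primary as a full alternative.
- *The CM power cannot be checked either.* This stands, since no SD is given. Confining the 80% to CM narrows the plan's claim without confirming it.
- *Calling a non-significant result inconclusive can be left to the analysis plan or report.* Often so, but a low-powered primary makes it worth stating here.

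**Conclusion.** The concern holds. The 80% power in Section 2.8 does not belong to the primary outcome declared in Section 2.7, and no retear effect is specified anywhere in the article. Assuming 27% control retear, 50 analysed per arm and a two-sided 5% test, power for a halving is about 40% (39% by normal approximation, 31% with Fisher). Reaching 80% needs a PRP retear rate of about 7% by exact chi-square, 6.4% by normal approximation or about 5% with Fisher, which is a relative reduction of roughly 74% to 81%. The exact percentages depend on the assumed control rate; the shortfall for a halving does not, within the 15% to 50% range examined. This must be corrected, because the only power claim in the article is attached to the wrong comparison.

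**What to change.** Choose one of two routes.

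1. **Keep retear as primary.** In Section 2.8, say that the 80% refers only to CM at 48 months. Add the power for retear with its assumptions: with 27% control retear, 50 per arm and a two-sided 5% test, about 80% for 27% v 7% and about 40% for 27% v 13.5%. Name the test used and show other control rates, since 27% is a background figure. State that a non-significant retear result will be reported as inconclusive, with its confidence interval.
2. **Realign the primary.** Before any outcome is seen, make CM at 48 months the primary outcome in Section 2.7 and retear the key secondary.

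Under either route, Section 2.8 should give the SD behind the CM calculation and an alpha that agrees with Section 2.9, so that the 80% can be checked.

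The cost is wording in Sections 2.7 and 2.8 and an update to the registry entry. No extra patients are needed. Under the first route, the sponsor has to state a less favourable power for the primary outcome.

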### Statistical analysis

2.9

The standard deviation and mean are the descriptive statistics. The normality of all the data was detected via the Kolmogorov–Smirnov test. The difference of value before and after the treatment was calculated by the paired sample *t* test. The student *t* test was applied for the comparison of variances between study group and control group. The analysis is implemented with the SPSS 16.0 (SPSS Inc., Chicago, IL), the significance level remain at *P* < .05.

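### CM, ASES and NRS: the paired before/after t test cannot inform the effect of PRP, and the between-arm t test, though valid, makes no adjustment for the baseline score that is collected

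*Protocol article*

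**What the plan says.** Protocol article, section 2.9 (Statistical analysis), names two inferential tests. For change over time: "The difference of value before and after the treatment was calculated by the paired sample" t test. For the arms, the Student t "test was applied for the comparison of variances between study group and control group". A t test compares means, so the word variances there must be loose wording. No baseline covariate, ANCOVA or repeated-measures model is named, and section 2.9 does not list the outcomes to which each test applies. CM, ASES and NRS are the only continuous before/after outcomes the article describes.

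Section 2.7 (Outcomes measures) shows that baseline values will exist: "All patients were evaluated at follow-up and baseline for the scores of Constant-Murley (CM) and American Shoulder and Elbow Surgeons (ASES), the numerical rating scale". For ASES and CM it adds that "the assessment are performed at baseline, 12 months, 24 months, and 48 months". The sentence ties those visits clearly only to ASES and CM; the NRS times are not clearly stated.

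Section 2.7 also states: "The primary outcome is retear rate". Section 2.8 (Sample size calculation) nevertheless sizes the trial on a CM difference of at least 5 points at 4 years, with 50 patients per group.

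**The concern.** The objective is to compare repair with PRP against repair without it. Under section 2.5 both arms have the arthroscopic repair, and controls receive saline by the same method. A paired test within an arm measures surgery, recovery and regression to the mean together. It contains no contrast between arms, so no result from it can support or refute a PRP effect.

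The between-arm t test does address the objective, but it makes poor use of the baseline score. On follow-up values, it leaves in the residual the variation that baseline could explain. On changes, it subtracts the whole baseline value whatever the correlation, which adds noise when the correlation is low. ANCOVA estimates the weight that baseline should carry, and in large samples is at least as precise as either.

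At stake is precision for the continuous scores, one of which (CM) is the outcome the trial was sized on. The tests are fixed in the article itself, so this is not a detail it leaves to another document.

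**Working it through.** **Inputs from the protocol article.** 50 per arm before loss, a CM difference of 5 points at 4 years and 80% power (section 2.8); significance level 0.05 (section 2.9); allocation 1:1 (section 2.3).

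**Assumptions, not in the document.** Two-sided testing; the SD; the baseline-to-follow-up correlation r, taken over 0 to 0.7; equal SD at baseline and follow-up. Section 2.8 reads "80% statistical power at an alpha level of 0.05" followed by a percent sign. I take 0.05, in line with section 2.9.

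**Step 1: the plan's own figure.** The 50 per arm cannot be reproduced because no SD is given. It can only be solved backwards:

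SD = 5 / [(1.960 + 0.842) × √(2/50)] = 5 / (2.802 × 0.2) = 8.92.

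With the exact t distribution the SD is 8.84. If 0.05% is read literally (two-sided 0.0005), the normal formula gives 5.78 instead.

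**Step 2: formulas.** For each analysis, power = Φ(5 / (s × 0.2) − 1.960), where s is:
- follow-up values, unadjusted: s = SD
- ANCOVA with baseline: s = SD × √(1 − r²)
- change scores: s = SD × √(2(1 − r))

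Example, ANCOVA at r = 0.5: s = 8.92 × √0.75 = 7.73; 5 / (7.73 × 0.2) = 3.235; 3.235 − 1.960 = 1.275; Φ(1.275) = 0.899.

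**Step 3: results at 50 per arm.**

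| r | t test on follow-up values | t test on changes | ANCOVA | n per arm for 80% power with ANCOVA |
|---|---|---|---|---|
| 0 | 80.0% | 50.8% | 80.0% | 50 |
| 0.2 | 80.0% | 60.1% | 81.6% | 48 |
| 0.3 | 80.0% | 65.8% | 83.6% | 46 |
| 0.5 | 80.0% | 80.0% | 89.9% | 38 |
| 0.7 | 80.0% | 95.1% | 97.5% | 26 |

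The power figures are the same to one decimal with the noncentral t and SD 8.84, including when ANCOVA is charged one degree of freedom for the covariate.

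Against follow-up values, ANCOVA gains 0, 1.6, 3.6, 9.9 and 17.5 points of power as r rises. Against change scores it gains 29.2, 21.5, 17.8, 9.9 and 2.4 points. At r = 0.5 its precision matches an unadjusted trial of 50 / (1 − 0.25) = about 67 per arm.

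**Step 4: the paired tests.** Two arms were simulated with no difference between them (50 per arm, SD 8.92, r = 0.5, 20,000 trials):

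| True improvement in both arms (CM points) | Exactly one arm significant | Both arms significant |
|---|---|---|
| 2.5 | 49.8% | 24.4% |
| 3.0 | 45.7% | 41.6% |
| 3.5 | 35.3% | 59.6% |
| 20 | 0% | 100% |

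Discordant results are common when improvement is small and vanish when it is large. In neither case do the paired tests carry information about PRP.

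**The case against.** The strongest reply is that nothing here is invalid. A Student t test between randomised arms keeps its type I error, and chance baseline imbalance is already covered by that error rate. This stands: the point is about efficiency, not bias. A reader might infer that imbalance would go uncorrected and distort the result; the document does not support that.

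Second, the text does not settle whether the between-arm test uses follow-up values or changes. It follows directly after the sentence on before/after differences, so changes are a fair reading. It would therefore be too strong to say that the test ignores baseline. The recommendation survives either reading, because ANCOVA is not beaten by either option in the table.

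Third, the size rests on an SD and a correlation that the document does not give. The interval from baseline to final follow-up spans surgery and four years, so a low correlation cannot be excluded. If follow-up values are compared, the gain is then only 1.6 points at 0.2 and nil at 0. This stands, and it is why a range is shown.

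Fourth, two further inferences are tempting. One is that a significant result in the PRP arm alone would be read as efficacy. No section says that PRP efficacy will be judged from the paired tests, a separate between-arm test is planned, and discordance is likely only if improvement after surgery is small. The other is that patients lost before 48 months would have their earlier visits discarded. Section 2.8 allows that "10% of data may be lost", but no rule for missing data is stated, so this describes a default and not the plan.

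Finally, retear rate is the declared primary outcome, so these scores are not primary. This limits the consequence but does not remove it, since section 2.8 rests on CM.

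**Conclusion.** The point holds as one of efficiency and relevance. The paired before/after test cannot inform the PRP effect and should not serve as an inferential analysis. The between-arm t test is valid but gives away precision that the collected baseline scores could supply. Under two-sided alpha 0.05 and the back-solved SD of about 8.8, ANCOVA raises power from 80% to about 82%, 84%, 90% and 97.5% at correlations of 0.2, 0.3, 0.5 and 0.7 if follow-up values would otherwise be compared, with no gain at 0. If changes would be compared, the starting point is about 51%, 60%, 66%, 80% and 95% at correlations of 0, 0.2, 0.3, 0.5 and 0.7. These figures illustrate a range; they are not demonstrated losses. The document supports neither inflated error from the t test nor a stated intention to claim efficacy from within-arm tests. Importance is moderate.

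**What to change.** In section 2.9, make the inferential analysis of CM, ASES and NRS the between-arm difference at 48 months (for NRS, at its final follow-up), with 95% CI, from ANCOVA with the baseline score as covariate. For scores measured at 12, 24 and 48 months, a mixed model with arm, visit, arm-by-visit and baseline score is an alternative. It would also use the earlier visits of patients lost later. State that before/after changes within each arm are reported descriptively only.

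The cost is wording: baseline scores are already collected, and no extra visits, data or patients are needed.

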## Discussion

3

The objective of this prospective randomized research is to study and then compare the long-term effectiveness of the repair of arthroscopic rotator cuff without and with the platelet-rich plasma. It is assumed that there is no difference in the clinical results between patients receiving the repair of arthroscopic rotator cuff and the patients who do not receive PRP enhancement. One limitation of this experiment is that the quantity of growth factors and the number of platelets exist in the activated platelet-rich plasma was unknown. The results of this study will provide useful new information on whether PRP is effective in the arthroscopic rotator cuff repair patients.
